#### Secondary analyses of the primary outcome

The primary analysis will be repeated as described with the PP population. In addition, the effect of treatment setting on the efficacy of PIP will be investigated by means of a moderator analysis. Moderators show their effect in the interaction with treatment group. Thus, the model will include all variables as described for the primary analysis with the addition of the treatment*setting interaction. Additional moderator analyses regarding the effectiveness of PIP including maternal attachment style and reflective functioning (AAI) as moderators will be calculated. A sensitivity analysis of the primary outcome will be computed using multiple-imputation methods and the PP population adjusted for maternal sensitivity at baseline and treatment setting as stratification variable. In a further sensitivity analysis of the primary outcome, a hierarchical regression model will be calculated which, in addition to the adjustment for the baseline values and the treatment setting, will include the therapists who performed the intervention in the model. Both sensitivity analyses will be repeated using also study center as stratification variable.

Linear ,mixed models for longitudinal data will be used to examine the change of the primary outcome across all measurement time-points for the treatment groups. The model will include predictors for treatment group and time as fixed effects as well as the treatment group × time interaction, baseline maternal sensitivity as covariate, treatment setting as stratification variable, and subjects as random effects. The therapists and further predictors will be added to the model when indicated by goodness-of-fit model comparisons (based on Akaike Information Criterion (AIC) values). All secondary analyses of the primary and secondary outcomes are considered exploratory.

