### Samples size calculations and statistical analyses

A power analysis [G*Power] based on a reported moderate to large effect size of Cohen’s *d* = 0.64 for a difference in maternal sensitivity after 6 weeks of intervention between the intervention group and the CAU group [19] and two-tailed testing with a significance level of *α* = 5% using an analysis of covariance (ANCOVA) (with maternal sensitivity at T1 as the dependent variable and maternal sensitivity at T0 as a covariate) resulted in a required sample size of *n* = 70 (per group) to detect an effect with a power of 95%. With an assumed drop-out rate of about 20% [1] the sample size calculates to *n* = 90 per group (total sample size *n* = 180 mother-child-dyads).

The statistical analysis will be carried out at the end of the last follow-up assessment and all analyses will be conducted in accordance *with intention-to-treat (ITT)* principles and will be including all randomized mother-child-dyads in the study. The *Full Analysis Set (FAS) will be used for all analyses (unless otherwise stated),* it will include all randomized mother-child-dyads. Data will be analyzed according to randomization irrespectively of the treatment received. Data from mother-child-dyads that have withdrawn from the study will be included in the FAS up to the date of their termination. The *Per-Protocol (PP) population* will comprise a subset of the FAS. It will consist of mother-child-dyads who will have received treatment according to the randomization, will have adequate therapy adherence, and no major protocol violations. Major protocol violations will be considered as not meeting all inclusion criteria, a change of treatment group or as the PIP intervention that has not been carried out properly according to the treatment manual. The *safety population* will include mother-child-dyads who have participated in at least one intervention session. Participants in the safety population will be analyzed according to the treatment actually received.

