#### Primary analysis of the primary outcome

The evaluation of the primary outcome (EAS, maternal sensitivity at T1) will be performed by a covariance analysis (ANCOVA) with the independent variable treatment (PIP vs. CAU), adjusted for maternal sensitivity at baseline (T0) and treatment setting as stratification variable based on the FAS population. Adjusted mean values of treatment groups with 95% confidence intervals and *p* value (two-sided) for group comparisons will be presented.

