#### Missing data

Analyses of primary and secondary endpoints will be conducted based on the FAS population without imputation of missing data. A sensitivity analysis is computed by imputing missing data of the primary outcome with multiple-imputation methods for linear regression using Markov chain Monte Carlo (MCMC) simulations. The selection of imputation variables will be decided blinded to treatment allocation and at least 5000 iteration and 100 imputations will be used.

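### The multiple-imputation check of the primary outcome is tied to the per-protocol set in one section and by default to the full analysis set in another; only the latter can test the ITT estimate

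*Protocol article*

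**What the plan says.** All statements are in the protocol article.

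- **Samples size calculations and statistical analyses.** All analyses are to follow ITT and "will be including all randomized mother-child-dyads in the study". The FAS, which contains every randomised dyad, "will be used for all analyses (unless otherwise stated"). On withdrawals: "Data from mother-child-dyads that have withdrawn from the study will be included in the FAS up to the date of their termination". The PP set is a subset of the FAS: dyads treated as randomised who "will have adequate therapy adherence, and no major protocol violations". Major violations are failing an inclusion criterion, changing treatment group, or a PIP course not delivered as the manual requires.
- **Primary analysis of the primary outcome.** An ANCOVA of T1 sensitivity, "adjusted for maternal sensitivity at baseline (T0) and treatment setting as stratification variable based on the FAS population".
- **Missing data.** "Analyses of primary and secondary endpoints will be conducted based on the FAS population without imputation of missing data". The next sentence adds: "A sensitivity analysis is computed by imputing missing data of the primary outcome with multiple-imputation methods for linear regression". No analysis set is named for this second analysis.
- **Secondary analyses of the primary outcome.** The section opens with a repeat of the primary ANCOVA in the PP set. It then says: "A sensitivity analysis of the primary outcome will be computed using multiple-imputation methods and the PP population", adjusted for baseline and setting. A second sensitivity analysis adds the therapists. A later sentence refers to the sensitivity analyses as a pair, both to be rerun with study center. A linear mixed model over all three time-points follows. All of these are labelled exploratory.

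**The concern.** An ANCOVA of T1 on T0 without imputation can use only dyads with both values. The promise to include all randomised dyads therefore does not describe the primary analysis, and the MI analysis is what should show whether the omission matters. Such a check should keep the population fixed and vary the missing-data handling.

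MI on the PP set varies both. It first removes dyads by what happened after randomisation. Manual-conform delivery of PIP is a criterion that only the PIP arm can fail. A dyad that stops PIP early may well lack both adequate adherence and a T1 video, so the PP set may discard dyads that imputation is meant to bring back. Agreement with the primary result would then not show that the ITT estimate is robust, and disagreement could not be put down to missing data.

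At stake is the one described imputation check on the sole primary outcome of an open trial that expects to lose about a fifth of its participants.

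**Working it through.** **Step 1: the plan's own figure.** Inputs from the sample-size section: 70 evaluable dyads per group, 20% drop-out, 90 per group stated.

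- 70 / (1 − 0.20) = 87.5, rounded up to 88 per group. The stated 90 is reproduced to within 2 per group, so the 20% is used as loss to the T1 analysis.

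**Step 2: who enters the primary ANCOVA.** Taking drop-out to mean no usable T1 sensitivity:

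- missing: 0.20 × 180 = 36 dyads
- analysed: 180 − 36 = 144 dyads (72 per group if the loss is equal)

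T0 is taken after randomisation (Trial design), so it can be missing too and would add to the 36. A dyad that withdraws before T1 may have data in the FAS but contributes nothing to this model.

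**Step 3: is this a power problem?** No. With Cohen's *d* = 0.64 (*f* = 0.32), two-sided 5% and one covariate, a noncentral-*F* calculation gives about 96.8% power for 144 dyads, against the planned 95%. The question is one of bias and analysis set.

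**Step 4: which set does the MI analysis use?**

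| Section | Set for MI |
|---|---|
| Secondary analyses of the primary outcome | PP, named in the sentence |
| Missing data | none named; FAS by the general default |

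The first section could be read as listing two analyses, one with MI and one in the PP set. Two features speak against that. The PP repeat has already been listed separately, so it would appear twice. The later reference to a pair of sensitivity analyses fits only if MI-with-PP is one and the therapist model is the other.

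**Step 5: how many dyads each version covers.** MI on the FAS covers all 180, provided missing T0 values are imputed as well. MI on the PP set covers only the PP dyads. The protocol gives no PP share, so the range is assumed:

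| PP share of FAS (assumed) | Dyads in MI on PP | Randomised dyads left out |
|---|---|---|
| 90% | 162 | 18 |
| 80% | 144 | 36 |
| 70% | 126 | 54 |
| 60% | 108 | 72 |

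**Step 6: possible bias, illustration only.** If the loss is equal in both arms and the treatment contrast among drop-outs differs from that among completers by Δ, the complete-case estimate is off by 0.20 × Δ. An assumed Δ of 0 to 0.5 SD gives 0 to 0.20 × 0.5 = 0.10 SD, at most 0.10 / 0.64 ≈ 16% of the planning effect. The document does not supply Δ or its sign.

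**The case against.** - **The Missing data section already plans MI on the FAS.** It names no PP restriction, follows directly on a sentence about the FAS, and the FAS is the default set. This stands as far as it goes. A reader might infer that the only missing-data check is on the PP set; the document does not settle that. It gives two incompatible answers for what appears to be the same analysis.
- **The mixed model covers the gap.** A reader might infer that no planned analysis goes beyond complete cases. That is too absolute. The mixed model is on the FAS by default and keeps dyads seen at 12 months but not at T1. It still omits dyads with no sensitivity measurement, loses those with T0 only if baseline enters solely as a covariate, and is not presented as a missing-data check.
- **PP exclusions are not purely one-sided.** Correct. Failing an inclusion criterion or changing group can happen in either arm. Manual-conform delivery applies to PIP alone. The only adherence instrument described is completed by PIP therapists, but the PP definition does not limit adherence to one arm. That the selection favours PIP is plausible, not shown.
- **The PP repeat without MI separates the two effects.** In part. FAS against PP shows the selection, and PP against PP with MI shows imputation within PP. Neither shows what imputation does to the FAS estimate.
- **A complete-case ANCOVA with inflated sample size is a conventional primary analysis.** Agreed. The choice of primary analysis is not the fault; the description of its population and the set for its check are.

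**Conclusion.** The point holds as a conflict that needs correcting. Followed as written, the section on secondary analyses puts MI on the PP set, where it cannot show whether the FAS estimate is robust to missing data. The Missing data section, read with the FAS default, implies an analysis that could. In addition, the statement that all randomised dyads are included does not fit a primary ANCOVA expected to use about 144 of 180, assuming the planned 20% drop-out means missing T1 sensitivity.

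No stated figure changes, and power is not in question. A reader might infer a definite bias in favour of PIP. The document does not support a size or a direction: the contrast among drop-outs, the share failing PP and the outcomes of those dyads are all unknown. Nor would standard MI on the FAS remove every bias, since it corrects only as far as the observed variables explain the loss. It would, however, be a check on the right population.

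**What to change.** Three changes of wording:

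1. In Secondary analyses of the primary outcome and in Missing data, state that the MI sensitivity analysis is run on the FAS: all randomised dyads, in the arm to which they were randomised. The planned rerun with study center then uses the same set.
2. Keep the PP repeat of the primary ANCOVA as a separate analysis and remove the PP set from the MI sentence.
3. Describe the primary ANCOVA as using FAS dyads with observed T0 and T1 sensitivity, so that it no longer reads as covering every randomised dyad.

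The imputation variables can stay with the blinded selection already planned. The cost is editorial: sample size, data collection and the primary model are unchanged, and at least 100 imputations are already planned. The protocol foresees no interim analysis and unblinds outcome data only after the last participant has finished. If made before that point, the change carries no risk of a data-driven choice.

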### Trial design

The study will be designed as a two-arm, open, multi-center RCT with parallel groups and blinded endpoint assessment (PROBE design; prospective, randomized, open, blinded endpoint) with 6 weeks of intervention.

Depending on the severity of the psychopathological symptoms and in agreement with the participants’ preferences, the decision for a particular treatment setting (inpatient or outpatient) will be made before randomization. After assignment to treatment setting, participants will be randomly allocated to either the PIP intervention group or the CAU control group. A biometrician will independently carry out a 1:1 block randomization with variable block length and stratification by setting (inpatient or outpatient) and study center. Treatment allocation is masked to the assigning personnel and there will be no special criteria for discontinuing or modifying the allocated intervention. Data of mothers and children will be assessed at three measurement points (see Fig. 1): at baseline after randomization and immediately before the intervention (T0), after the intervention at 6 weeks (T1) and at 12-month follow-ups (T2). Study centers are located in the German cities Berlin and Flensburg. At the time of writing additional effort is being made for a study center in Hamburg.

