### Assessment and outcome measures

#### Primary endpoint

*Maternal sensitivity*: the primary outcome of the current study will be maternal sensitivity at the end of 6-week intervention (T1) measured by the Emotional Availability Scale (EAS). EAS [36] is a widely used assessment for the quality of mother-child interaction with excellent psychometric properties. Fifteen-minute videotaped dyadic free-play interactions will be assessed at the mother’s home environment and will be coded by independent and reliable coders blind to treatment allocation. EAS will be assessed at all three measurement time-points and will be coded using a Likert Scale (1 to 7) on maternal sensitivity as well as three further maternal dimensions (structuring, non-intrusiveness and non-hostility) and two child dimensions (responsiveness to parent and involvement with parent).

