#### Analyses of the secondary outcomes

Secondary outcomes will be computed according to the analysis strategy of the primary outcome using ANCOVA or logistic regression (depending on the scale of the respective outcome, continuous or dichotomous). Likely moderators will be added to the models including setting, and maternal attachment style and AAI reflective functioning. In order to investigate the longitudinal course until the 12-month follow-up, linear mixed models will also be calculated for the change of secondary outcomes (e.g., EPDS, PSI and PRFQ). In addition, sensitivity analyses are planned for the health economic analyses, in which the underlying unit-cost assumptions will be varied within realistic ranges.

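### As written, the exploratory longitudinal mixed model uses T0 sensitivity both as a response and as a covariate, so the covariate does nothing for the group × time contrast

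*Protocol article*

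**What the plan says.** The Protocol article, under Secondary analyses of the primary outcome, plans linear mixed models for longitudinal data to "examine the change of the primary outcome across all measurement time-points for the treatment groups". It lists the terms: "predictors for treatment group and time as fixed effects as well as the treatment group × time interaction", then "baseline maternal sensitivity as covariate, treatment setting as stratification variable, and subjects as random effects". The same section closes with "All secondary analyses of the primary and secondary outcomes are considered exploratory".

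The time points are fixed elsewhere. Trial design states "Data of mothers and children will be assessed at three measurement points" and gives the first of them as "at baseline after randomization and immediately before the intervention (T0"; T1 is at 6 weeks and T2 at the 12-month follow-up. Primary endpoint adds "EAS will be assessed at all three measurement time-points". Nothing in the analysis sections restricts the mixed model's responses to T1 and T2.

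Analyses of the secondary outcomes says "linear mixed models will also be calculated for the change of secondary outcomes", with EPDS, PSI and PRFQ as examples, and lists no model terms.

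The primary analysis is an ANCOVA of T1 sensitivity with T0 sensitivity and setting as covariates. There T0 appears on the right-hand side only.

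**The concern.** A baseline value can be handled in two sound ways in a repeated-measures model: as a covariate for the later responses, or as one of the responses. The listed terms do both at once. Given the covariate, the T0 response is known exactly, while T1 and T2 still vary. One common baseline slope then has to serve a visit where the true slope is 1 and two visits where it is the ordinary T0–T1 and T0–T2 regression slope.

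At stake is the model meant to describe the course of sensitivity to 12 months. Its change contrast would lose the precision that baseline adjustment is there to give, and some of its standard errors could be too small. The confirmatory T1 comparison does not depend on it.

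**Working it through.** **Inputs.** From the document: three measurement points, the listed model terms, 90 dyads per arm and about 20% drop-out, so 90 × 0.8 = 72 completers per arm; d = 0.64. Assumed, because the document gives no values: SD 1 at each visit; common correlation r = 0.3, 0.5 or 0.7 between visits; a subject-level random intercept with constant residual variance. There is no figure in the plan for this model to reproduce.

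**1. Group × T1 contrast.** The T0 covariate is constant within a dyad, so it drops out of every within-dyad difference. With complete data and a random intercept, the group × T1 estimate is therefore (mean T1 − T0 change in PIP) − (mean T1 − T0 change in CAU). In 2,000 simulated data sets per setting the two agreed to within 2 × 10⁻¹⁴.

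**2. Its precision against ANCOVA.**
- Change score: variance = (2/72) × 2(1 − r)
- ANCOVA: variance = (2/72) × (1 − r²)
- Ratio = 2(1 − r)/(1 − r²) = 2/(1 + r)

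| r | SD change score | SD ANCOVA | Variance ratio |
|---|---|---|---|
| 0.3 | 0.197 | 0.159 | 1.54 |
| 0.5 | 0.167 | 0.144 | 1.33 |
| 0.7 | 0.129 | 0.119 | 1.18 |

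The simulation gave SDs of 0.201 / 0.169 / 0.131 against 0.161 / 0.147 / 0.121. Power at d = 0.64 was 0.911 / 0.969 / 0.999 against 0.976 / 0.991 / 1.000. The contrast kept a correlation of −0.60 / −0.51 / −0.40 with the chance difference between arms at T0. Its type I error under equal correlations was 0.058, close to nominal.

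**3. Group difference at T1 (group + group × T1).** The common baseline slope is the average over the three visits, b = (1 + 2r)/3 = 0.533 / 0.667 / 0.800, against true slopes at T1 of 0.3 / 0.5 / 0.7. This is over-adjustment. For r = 0.5:
- Residual variance at T0: (1 − 0.667)² = 0.111
- Residual variance at T1 and at T2: 1 − 2(0.667)(0.5) + 0.667² = 0.778
- The model pools these: (0.111 + 0.778 + 0.778)/3 = 0.556, so the reported SE = √(2 × 0.556/72) = 0.124
- Actual SD = √(2 × 0.778/72) = 0.147
- Type I error = 2[1 − Φ(1.96 × 0.124/0.147)] ≈ 0.10

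The simulation gave SE 0.141 / 0.125 / 0.100 against SD 0.166 / 0.149 / 0.122, and type I error 0.099 / 0.102 / 0.113.

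**4. Group × T1 when correlations differ.** Assume r(T0,T1) = r(T0,T2) = 0.5 and r(T1,T2) = 0.7. The variances of the three pairwise within-dyad differences are 1.0, 1.0 and 0.6, mean 0.867. The reported SE is √(2 × 0.867/72) = 0.155; the true SD is √(2 × 1.0/72) = 0.167. Type I error = 2[1 − Φ(1.96 × 0.155/0.167)] ≈ 0.07.

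**5. T1 and T2 as responses, T0 as covariate.** Under equal correlations, the treatment effect at T1 had SD 0.161 / 0.146 / 0.121 and mean SE 0.159 / 0.145 / 0.120. Type I error was about 0.06, power equalled that of ANCOVA, and correlation with baseline imbalance was about −0.02.

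**The case against.** The article never writes out the response vector. Change could be read as T1 and T2 values adjusted for T0, which is how the primary ANCOVA treats baseline, and the authors may have meant that. But it is not what the words say: all time-points are named, and two other sections count T0 among them. Because the terms are listed, this is a conflict in a stated rule and not detail left to an analysis plan.

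Several stronger readings are tempting, and the documents do not support them:

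- **That baseline adjustment is cancelled throughout.** This is exact only for group × time with complete data. The group difference at T1 is over-adjusted instead. With about 20% random drop-out, a short simulation put the group × T1 estimate on average 0.018 SD (at most 0.05) from the completers' change-score difference: close, but not identical.
- **That the model answers a different question from the ANCOVA.** T0 precedes the intervention in a randomised trial, so both target the same expected effect. They differ in precision and in their handling of chance imbalance.
- **That the covariance is misspecified as a matter of fact.** The text says only that subjects are random effects. A random intercept with constant residual variance is an assumption, and a condensed article may leave the covariance structure to a fuller document.
- **That a type I error of 7% is established for group × time.** It belongs to one assumed correlation pattern. With equal correlations the error was near nominal, and another assumed pattern (0.5 for T0–T1, 0.3 for T0–T2, 0.5 for T1–T2) gave 3.7% at T1 and 8.2% at T2.
- **That EPDS, PSI and PRFQ share the fault.** The mixed models for them are announced without terms, so carry-over is an inference.
- **That nothing else covers 12 months.** The T2 sensitivity responder variable and the attachment classification are analysed without this model.

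The exploratory label also stands, and it limits the weight of the point.

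**Conclusion.** The specification is wrong as written: T0 sensitivity is on both sides of the longitudinal model. The loss of baseline adjustment in the group × time contrast follows from the listed terms, given complete data and a random intercept. Its cost is a variance 18% to 54% above ANCOVA's over the assumed range of r, plus retained sensitivity to chance imbalance; there is no bias. The SE problems (type I error about 10% for the group difference at T1, and about 7% for group × time in one assumed pattern) rest further on the assumed random-intercept covariance and correlations. The primary ANCOVA is unaffected. This is a modest but real error, worth correcting before the data are unblinded.

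**What to change.** State the responses explicitly, in one of two ways:

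1. T1 and T2 sensitivity as responses, T0 sensitivity as covariate, preferably with a T0 × time term; or
2. T0, T1 and T2 as responses, with the T0 mean constrained equal across arms and no T0 covariate.

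In either case, name the within-dyad covariance; an unstructured one avoids relying on equal correlations. If the same model is meant for EPDS, PSI and PRFQ, say so under Analyses of the secondary outcomes and specify it in the same way.

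The cost is a change of analysis wording. No new data, visits or sample size are needed.

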### Intervention

*Focused Parent-Infant-Psychotherapy* is a psychotherapeutic intervention in which mother-child-dyads are treated together. Individual sessions could also be held together with the father. PIP aims at fostering the parent-infant-relationship by supporting the parents’ ability to understand and mentalize the child’s affective states. It aims at promoting parental self-reflection and sensitivity to support the building and maintaining of parent-infant-relationships. PIP interventions are exclusively delivered by trained and supervised psychotherapists who are additionally certified in the PIP method. The manualized PIP ([name], [name], [name]: SKKIPPI-Studymanual for Parent-Infant-Toddler-Psychotherapy (PIP), unpublished) is a focused psychodynamic intervention with 12 succeeding sessions of approx. 50 min in 6 weeks (two sessions per week). The aims of PIP are clarification of problems, affect regulation, self-reflection, a change of perspective and the activation of the participants’ interpersonal resources. The intervention includes a mentalization-based approach, and works with reframing, an appropriate confrontation within a supportive framework, psychoeducation, the development of action strategies, and video-feedback. To enhance manual adherence, all study therapists will be additionally trained in the manual before the start of the treatment.

The inpatient treatment is characterized by interventions in adult psychiatric departments with MBUs or day hospitals. In inpatient settings, PIP will be provided in addition to standard therapeutic care. In outpatient settings PIP will be provided in the patients’ home environment or in psychiatric outpatient departments.

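### The confirmatory ANCOVA and the power calculation treat PIP dyads as independent although they share therapists; therapist enters only in exploratory models, one of them by AIC selection

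*Protocol article*

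**What the plan says.** All references are to the protocol article.

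- *Intervention*: "PIP interventions are exclusively delivered by trained and supervised psychotherapists". *Control* describes CAU as a mixed set of standard services, with no common provider level.
- *Samples size calculations and statistical analyses*: the calculation uses a Cohen's d of 0.64 "for a difference in maternal sensitivity after 6 weeks of intervention between the intervention group and the CAU group", "two-tailed testing with a significance level of" 5%, and an ANCOVA "with maternal sensitivity at T1 as the dependent variable and maternal sensitivity at T0 as a covariate". It arrives at 70 ("per group) to detect an effect with a power of 95"%), raised to 90 per group for about 20% drop-out. It contains no ICC or design effect.
- *Primary analysis of the primary outcome*: a "covariance analysis (ANCOVA) with the independent variable treatment (PIP vs. CAU"), adjusted for T0 sensitivity and setting. There is no therapist term.
- *Secondary analyses of the primary outcome*: therapist appears twice. A hierarchical regression, run as a sensitivity analysis, "will include the therapists who performed the intervention in the model"; no condition is attached, and it is repeated with study center. For the longitudinal mixed model, "The therapists and further predictors will be added to the model when indicated by goodness-of-fit model comparisons", judged by AIC. The section classes all of these analyses as exploratory.

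**The concern.** If therapists differ in the results they obtain, two PIP dyads with the same therapist are more alike than two with different therapists. The PIP mean then varies more than an independent-observations model allows, and the CAU mean does not. The planned ANCOVA would report too small a standard error for the treatment difference, so the one confirmatory p value would be too small and its confidence interval too narrow. Power worked out on the same assumption would be optimistic.

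The protocol recognises therapist effects, since it plans models for them, but keeps them out of the analysis on which the trial's conclusion rests. In the longitudinal model it makes the correction depend on a fit criterion. With few therapists, such a criterion often fails to detect a therapist variance that is nonetheless large enough to distort the standard error.

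**Working it through.** **Inputs from the protocol:** d = 0.64, two-sided alpha 0.05, 70 per group required, 90 per group randomized, about 20% drop-out (90 × 0.80 = 72 evaluable per arm).

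**Inputs assumed:** ICC 0.02 to 0.10 and 6 to 12 dyads per therapist (12 down to 6 therapists for 72 dyads). The protocol gives neither. That each therapist treats several dyads is itself an inference, but the planned therapist models make sense only if that is so.

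**Step 1. The plan's own figure.** With independent dyads, a noncentral t calculation, or the equivalent ANCOVA with f = 0.32 and one covariate, needs 65 per group for 95% power, against the stated 70. At 70 per group power is 96.4%, and at 72 it is 96.8%. The stated size therefore carries a small reserve. That difference is on the safe side and is not part of this point.

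**Step 2. Type I error of the planned ANCOVA.** With m dyads per therapist, the PIP-arm design effect is DE = 1 + (m − 1) × ICC. CAU keeps a design effect of 1, so the variance of the difference is inflated by V = (DE + 1)/2. The true two-sided error is 2[1 − Φ(1.96/√V)].

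Example, ICC 0.05 and m = 9: DE = 1 + 8 × 0.05 = 1.40; V = 2.40/2 = 1.20; 1.96/1.095 = 1.789; error = 7.4%.

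**Step 3. Power with clustering modelled.** With k therapists, SE² = (DE + 1)/72, and the Satterthwaite degrees of freedom are (DE + 1)² / [DE²/(k − 1) + 1/71].

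Same example, k = 8: SE = √(2.40/72) = 0.1826; 0.64/0.1826 = 3.505; df = 5.76/(1.96/7 + 1/71) = 19.6; critical value 2.089; power = 91.5%.

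| ICC | Dyads per therapist (therapists) | DE | V | True type I error | Power, V only | Power, V and small-sample df |
|---|---|---|---|---|---|---|
| 0.02 | 6 (12) | 1.10 | 1.05 | 5.6% | 96% | 95% |
| 0.05 | 9 (8) | 1.40 | 1.20 | 7.4% | 93.5% | 91.5% |
| 0.05 | 12 (6) | 1.55 | 1.275 | 8.3% | 92% | 88% |
| 0.10 | 12 (6) | 2.10 | 1.55 | 11.5% | 86% | 80% |

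The true standard error is √V times the reported one: 1.02 times in the first row and 1.24 times in the last.

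**Step 4. Check by simulation.** The unclustered ANCOVA was simulated with 70 per arm, 20,000 runs per setting and no treatment effect. For 6, 10 and 15 therapists, rejection rates were 6.2%, 5.6% and 5.6% at ICC 0.02; 8.4%, 6.5% and 6.0% at ICC 0.05; and 11.1%, 8.3% and 7.3% at ICC 0.10. These agree with the formula.

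**Step 5. The AIC rule.** A simplified simulation used one time point, 72 per arm, a real therapist variance in PIP only, no treatment effect and 8,000 runs per setting. AIC dropped the therapist term in 92% of runs (ICC 0.02, 12 therapists), 83% (ICC 0.05, 8 therapists) and 64% (ICC 0.10, 6 therapists). In the runs where it was dropped, the unclustered test rejected in 5.4%, 7.2% and 11.8%. The rule does not single out the data sets in which ignoring therapists is harmless. The longitudinal model has more structure than this, so these figures illustrate the mechanism and do not predict rates for the trial.

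**The case against.** The best defence is that therapists are not overlooked. A therapist-adjusted sensitivity analysis of the primary outcome is planned without condition. A manual, prior training and monthly supervision should keep therapist differences small. A simple primary model is also a reasonable preference when therapists may be few. Every magnitude above rests on an ICC and a therapist count that the protocol does not give. All of that is fair. It bears on the size of the effect, but it does not change the fact that the confirmatory interval has no allowance for therapists.

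Four stronger readings are tempting, and the protocol does not support them:

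- *The hierarchical model cannot fit a one-arm therapist structure.* Its structure is not stated. A random therapist effect confined to PIP is compatible with the text, and the reference to those who performed the intervention points that way. A fixed therapist factor would be aliased with treatment, but the protocol does not say it will use one. Such coding may sit in an analysis plan that is not shown.
- *AIC selection affects the primary result.* The AIC rule governs only the longitudinal mixed model, which is exploratory.
- *The 95% power is wrong outright.* At ICC 0.02 with about 12 or more therapists it holds, thanks to the reserve in the 70. The baseline covariate could also help. If d = 0.64 is on the unadjusted standard deviation (an assumption) and the ICC applies to the residual, a T0–T1 correlation of 0.3 brings the V-only power at ICC 0.05 and 9 per therapist back to about 95%: 72/(1.20 × 0.91) = 66 effective dyads per arm. That gain does not repair the type I error.
- *The result cannot be generalized beyond the therapists used.* This is too absolute for a manualized, supervised treatment with a planned therapist-adjusted analysis.

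**Conclusion.** The point holds in this form: the confirmatory ANCOVA and the power calculation assume independent dyads although PIP dyads share therapists. Therapist is handled only in exploratory analyses, and in one of these only if AIC favors it.

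Over the assumed range (ICC 0.02 to 0.10, 6 to 12 dyads per therapist, 72 evaluable per arm), the primary test's true error is about 5.6% to 11.5% against a nominal 5%. Power with clustering modelled is about 95% at the favorable end and about 80% at the other. With a low ICC and many therapists the problem is minor; with an ICC of 0.05 or more and few therapists it is material. Any positive ICC pushes the error in the same direction, above 5%. The change is worth making because it is cheap and protects the only confirmatory inference, but the design itself is not invalid.

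**What to change.** - Make the already planned therapist model the confirmatory analysis, written as a partially nested mixed ANCOVA: T0 sensitivity and setting as fixed effects, a random therapist effect in the PIP arm only, and Satterthwaite or Kenward-Roger degrees of freedom. Keep the plain ANCOVA as a sensitivity analysis.
- Keep the PIP-only therapist term in the longitudinal model regardless of AIC.
- State that the 95% power assumes no therapist clustering, give the expected number of therapists, and show power for ICC 0.02 to 0.10.

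Adjustment for study center and arm-specific residual variances are separate questions and are not needed for this correction.

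The cost is wording. The planned models already require therapist identity, no further dyads or assessments are needed, and outcome data stay blinded until the last participant finishes, so the change can be prespecified. The downsides are a somewhat wider confidence interval, a less favorable stated power, and fewer degrees of freedom if therapists are few. If the ICC is in fact zero, the formula in step 3 with DE = 1 gives 95.3% power with 6 therapists and 96.3% with 12, against 96.8% for the plain ANCOVA: a loss of at most about 1.5 points.
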